## Oversight and monitoring

### Composition of the coordinating center and trial steering committee {5d}

The team responsible for recruitment and administrative task of running the trial meets weekly. The group consists of the Principal Investigator, Project Manager, staff responsible for treatment and recruitment activities. No separate Trial Steering Committee is convened for this low-risk study. Independent safety oversight is provided by a statistician/monitor who conducts the prespecified interim safety reviews (see {21b}); the clinical team does not access comparative interim results unless unblinding is required to evaluate a safety signal. Qualitative input from the pilot phase (patients and clinicians) informed participant-facing materials, screening and reminder procedures, questionnaire burden/acceptability, and retention strategies.

### Composition of the data monitoring committee, its role and reporting structure {21a}

The intervention researched in the trial is of low risk, and the Human Research Ethics Committee does not require a Data Monitoring Committee. Independent safety oversight is nevertheless provided by a statistician/monitor who conducts the interim safety reviews described in.

### Adverse event reporting and harms {22}

Participants can report the occurrence of undesirable treatment effects at any point through the study period by alerting the designated therapist on the digital platform or assessor or contacting the study personnel. Weekly measures to capture any unwanted adverse events will be administered, including questions about intensity, duration, and characteristics of the adverse event.

All potential undesirable treatment effects will be categorized by the investigator into three levels: mild, moderate, or severe. An event will be deemed serious if it poses a life-threatening risk, leads to death, causes persistent or significant disability/incapacity, necessitates hospitalization or its prolongation, or is determined to be medically significant by the principal investigator. The Negative Effects Questionnaire (NEQ) will be utilized posttreatment and during follow-ups to systematically gather data on potential adverse effects.

Therapists will be needed to promptly inform the principal investigator if they have concerns that a participant has caused, or is at risk of causing, significant harm to themselves or others or discloses any suicidal ideation. In such cases, a suicide risk assessment will be conducted over the phone to ensure appropriate and immediate support.

All participants in the study will receive active treatments with previous support by clinicians who specialize in the treatment of PTSD. Previous studies that have investigated intensive prolonged exposure have not detected any serious adverse events. The additional risks associated with participating in digital HOPE are hence considered to be small. All participants will be closely monitored during the study, and additional treatment will be provided in case of an unlikely severe deterioration.

Excluded participants will be informed where to seek help in the regular health care system. After the 1-month follow-up, participants will be offered the treatment they were not originally allocated to.

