## Comparator

Active control will use established CBT interventions such as psychoeducation about trauma and PTSD, relaxation, stress management techniques, and controlled breathing but will not include any exposure. The treatment will be given in a digital format with therapist support and consist of six sequential treatment modules that the participants are expected to complete in 10 weeks.

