### Relevant concomitant care permitted or prohibited during the trial {11d}

As per the inclusion and exclusion criteria, the participant must have had a stable dose of any psychotropic medication for at least 4 weeks prior to study entry, and no other ongoing trauma-focused CBT or eye movement desensitization and reprocessing therapy is permitted during the trial. Data on any potential alterations to medication or the initiation of trauma-focused CBT or Eye Movement Desensitization and Reprocessing therapy will be collected during the follow-up assessment.

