## Assignment of interventions: Blinding

### Who will be blinded {17a}

Group allocation will be masked to the assessors up to completion of the 12-month follow-up. Participants will receive explicit instructions not to discuss their treatment allocation with the assessor. Following each assessment, the assessors will be requested to guess the participants’ allocation, and these responses will be compared to chance at the study’s conclusion to assess the integrity of blinding.

If participants inadvertently disclose the treatment allocation during the assessment, the assessment will stop, and another blind assessor will reassess the diagnosis. The participant will also be assigned another assessor at subsequent follow-ups. The primary outcome assessors and trial statistician will be blinded to group allocation during the whole duration of the trial.

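### Participants may report undesirable treatment effects to the masked CAPS-5 assessor, and the masking safeguards do not prevent the arm being inferred from such a report

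*Protocol article*

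**What the plan says.** Adverse event reporting and harms {22} gives participants three ways to report an undesirable effect of treatment at any point in the study: "by alerting the designated therapist on the digital platform or assessor or contacting the study personnel". It also describes weekly adverse event questions and the Negative Effects Questionnaire (NEQ), which Table 2 lists as self-rated.

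Who will be blinded {17a} states: "Group allocation will be masked to the assessors up to completion of the 12-month follow-up". It sets out these protections:

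- An instruction: "Participants will receive explicit instructions not to discuss their treatment allocation with the assessor".
- A remedy: "If participants inadvertently disclose the treatment allocation during the assessment, the assessment will stop, and another blind assessor will reassess the diagnosis". That participant then has a different assessor at later follow-ups.
- A check: "Following each assessment, the assessors will be requested to guess the participants’ allocation". The guesses are compared with chance when the study ends.

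The Comparator section says that the control programme uses psychoeducation, relaxation and stress management "but will not include any exposure".

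On concomitant care, {11d} says that medication changes and "the initiation of trauma-focused CBT or Eye Movement Desensitization and Reprocessing therapy will be collected during the follow-up assessment". It does not say who collects this or in what form.

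**The concern.** The primary outcome is a clinician-rated interview. Participants and therapists know the allocation, so masking the assessor is the main protection of the CAPS-5 score against detection bias. Section {22} nevertheless offers the assessor as someone to tell about unwanted effects of treatment. Such effects arise only after randomization, when the assessor is meant to be masked.

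The arms differ in exactly the feature that such a report may describe. A participant who mentions distress after an imaginal or in vivo exercise has not named an arm, but the assessor can work it out. At the 1-month endpoint this can point only to HOPE, because the other programme is offered only after that visit. The possible leak is therefore one-sided between arms at the time of the primary rating.

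**Working it through.** **1. Sections side by side.**

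| Question | Section | Answer |
|---|---|---|
| May the assessor receive reports of treatment effects? | {22} | Yes, at any point in the study |
| Is the assessor masked at that time? | {17a} | Yes, until the 12-month follow-up is complete |
| Is a separate, unmasked assessor defined? | Whole article | No |
| Can the content of a report imply the arm? | {6b}, Comparator | Yes, if it refers to exposure |
| Does the instruction to participants cover treatment effects? | {17a} | No, only allocation |
| Does stop-and-reassess cover an implied arm, or a report outside the interview? | {17a} | Not clearly; it is triggered by disclosure of allocation during the assessment |
| Does the allocation guess prevent inference? | {17a} | No; it measures lost masking afterwards |

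The first two rows conflict, and the last three show that the safeguards do not resolve the conflict.

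**2. The plan's own figure, as the base for an illustration.** With d = 0.35, two-sided α = 0.05, 80% power and 1:1 allocation (Sample size {14}), n per arm = 2(1.960 + 0.842)² / 0.35² = 128.1, rounded up to 129. This matches the stated 129, with power 0.80. The point does not depend on the sample size.

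**3. Illustration of size.** Suppose a share f of HOPE ratings is affected and each moves by b SD. Both are assumptions; the documents give neither.

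- Spurious difference: d* = f × b.
- Standard error of d with 129 per arm: √(2/129) = 0.1245.
- Type I error: 1 − Φ(1.96 − d*/0.1245) + Φ(−1.96 − d*/0.1245).
- Power at a true d = 0.35 if the shift works against HOPE: Φ((0.35 − d*)/0.1245 − 1.96).

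| f | b (SD) | d* | Type I error | Power if the shift is against HOPE |
|---|---|---|---|---|
| 10% | 0.2 | 0.020 | 0.053 | 0.755 |
| 10% | 0.35 | 0.035 | 0.059 | 0.716 |
| 20% | 0.35 | 0.070 | 0.087 | 0.614 |
| 20% | 0.5 | 0.100 | 0.127 | 0.519 |

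**4. The same idea in CAPS-5 points.** Assume that 5–20% of HOPE ratings are affected, by 2–4 points each, with an SD of 10–12.

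- Ratings affected: 0.05 × 129 to 0.20 × 129, about 6 to 26.
- Shift in the arm mean: 0.05 × 2 = 0.1 to 0.20 × 4 = 0.8 points.
- Target effect: 0.35 × 10 = 3.5 to 0.35 × 12 = 4.2 points.
- Ratio: 0.1/4.2 = 2% to 0.8/3.5 = 23%. The upper end combines every worst case.

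**5. Concomitant therapy.** Follow-up visits include both an interview and self-rated forms on the platform. The self-rated TIC-P at the same visits already covers medication and use of care. The wording of {11d} fits either mode of collection.

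**The case against.** The case on the other side is substantial, and much of it stands.

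- **The assessor is an optional route.** Systematic capture goes through the weekly platform question and the self-rated NEQ, and by the 1-month interview most complaints will have had another outlet. This stands and limits the likely frequency.
- **Not every report reveals the arm.** Poor sleep or increased distress could come from either programme, since the control also includes psychoeducation about trauma. This stands; only reports that point to exposure matter.
- **Keeping every contact open to harm reports is a defensible safety choice.** This stands for urgent disclosures, which the fix preserves.
- **An article leaves assessor scripts to the full protocol.** True of scripts. But naming the assessor as a reporting route is a rule the article states, not a detail it omits.

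A reader might also infer four stronger claims that the document does not support:

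- **That the masked assessor asks about new trauma-focused therapy.** Section {11d} does not say so, and it may be self-reported. Starting outside therapy does not in itself identify the arm. A control participant who has taken up HOPE could reveal it at 6 or 12 months, but that option opens only after the primary endpoint, and later follow-up is described as naturalistic.
- **That the assessor's is the only blind.** The trial statistician is blinded too, although that does not protect the rating itself.
- **That primary data will be lost.** Section {17a} provides for reassessment by another blind assessor. The burden of a second interview is real; missing data are conjecture.
- **That the bias favours HOPE.** Hearing of an unwanted effect could push a rating either way.

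**Conclusion.** The point holds for the conflict between {22} and {17a}. The protocol makes a masked rater a channel for information that can imply the arm, and its safeguards address explicit disclosure or later detection rather than inference. Severity is minor to moderate.

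The conflict itself rests on the text alone. The size does not: the share of ratings affected, the shift per rating, the SD and the direction are all assumed. Within the ranges shown, occasional reports would barely change the error rates and frequent ones would matter. The allocation guesses will indicate at trial level whether masking held, but cannot repair ratings already made. The wording on concomitant therapy in {11d} needs only clarification, mainly for the 6- and 12-month ratings.

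**What to change.** 1. In {22}, remove the masked assessor as a routine reporting route. Direct reports to the therapist, the platform (weekly question and NEQ) or unmasked study personnel. The assessor redirects non-urgent reports and passes urgent safety disclosures on at once.
2. In {17a}, extend the instruction to participants from allocation to treatment content and treatment effects.
3. In {17a}, apply the reassignment rule also when a report implies the arm, whether or not it is made during the interview.
4. As a clarification in {11d}, state that medication changes and new trauma-focused therapy are self-reported on the platform alongside the TIC-P.

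The cost is a few sentences, a line in the assessor briefing and a notice to participants. The downside is that one optional reporting route is narrowed; all the others are already in place. Inclusion is expected to run to August 2026 and follow-up to October 2027 (Trial status), so the change would protect the ratings still to come. The date of the change should be recorded so that allocation guesses before and after it can be compared.

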### Frequency and plans for auditing trial conduct {23}

Any potential modifications to the protocol will be fully disclosed on Open Science Framework and Clinicaltrials.org.

### Plans for communicating important protocol amendments to relevant parties (e.g., trial participants, ethical committees) {25}

If needed, amendments to the Swedish Ethical Review Authority will be submitted. Any potential modifications to the protocol will be fully disclosed on Open Science Framework and Clinicaltrials.org.

### Dissemination plans {31a}

Participants in a previous pilot study on HOPE were interviewed about their experiences, and some modifications were made to the treatment protocol accordingly. The obtained findings will have important implications for the treatment of PTSD, and the results hold great importance to a large target group consisting of afflicted individuals and their families, policy makers, clinicians, stakeholders, media, and the public. The results in the project will be communicated to the scientific community by publishing the results in open access, high-impact scientific journals and by presenting our results at several national and international key conferences. The results will further be communicated more widely according to a separate communication plan using state-of-the-art communication tools and help from a communication expert.

We aim to reach both professionals as well as a broad audience of anyone interested in the research project through each of the project’s parties’ websites, social media channels, press releases, local and national newspaper, TV, and radio coverage. Since regular health care is already involved in the project, implementation is expected to be straightforward.

## Discussion

The study is the first trial to evaluate a digital therapist-guided treatment for PTSD (HOPE) in a Swedish psychiatric setting and not exclude patients with severe or complex PTSD and has the potential to impact guidelines on its suitability for that target group. The study is well powered as a superiority trial, and the research group has extensive expertise in trauma and PTSD as well as digital interventions. The therapists and assessors engaged in the trial have undergone comprehensive training and supervision in the treatments being investigated and in the utilization of the clinical gold-standard measure employed to assess PTSD. Several measures to increase the scientific trustworthiness of the study have been taken. The study hypotheses and the data analytic plan were prospectively registered. The chosen outcome measures for the study are considered the gold standard. The results of the trial will be communicated in open access scientific publications, at scientific conferences as well as meetings with representatives from the health care system and patient organizations, and in public media. The trial will be conducted in a regular care setting, which could pose a problem. The therapists delivering the treatment work clinically at the recruitment site and currently have high caseloads, and taking part in the research is an additional responsibility. If a therapist does need to drop out of the study due to other work commitments or for personal reasons, it could take quite some time to recruit new clinicians to replace them and train them in the treatment and the measures used in the study.

In summary, previous work has shown that trauma focused online has the potential to be an effective treatment for PTSD. No study to date has yet compared digital prolonged exposure against an active control condition in a psychiatric setting with patients with moderate to severe PTSD.

## Trial status

Inclusion started on the 4th of September 2023 and is expected to end in August 2026. The last follow-up appointment is expected to take place in October 2027. Data analysis and reporting of results will begin when all data from the primary endpoint have been collected.

## Data Availability

The principal investigator [name] will serve as the data custodian. Deidentified datasets can be obtained from the principal investigator upon reasonable request and under formal data transfer agreements to facilitate additional research.

## Abbreviations

AQoL-6D: Assessing Quality of Life 6 Dimensions
CAPS-5: Clinician-Administered PTSD Scale for DSM-5
CIPE: Condensed internet-delivered prolonged exposure CIPE
CBT: Cognitive behavioral therapy
CEQ: Credibility/Expectancy Questionnaire
CHEERS: Consolidated Health Economic Evaluation Reporting Standards
CONSORT: Consolidated Standards of Reporting Trials
DSM-5: Diagnostic and Statistical Manual of Mental Disorders, fifth edition
EMDR: Eye Movement Desensitization and Reprocessing therapy
HOPE: Huddinge Online Prolonged Exposure
GCP: Good Clinical Practice
ITQ: The International Trauma Questionnaire
NEQ: Negative Effects Questionnaire
OSF: Open Science Framework
RCT: Randomized controlled trial
SUD: Subjective Units of Distress Scale
TIC-P: Treatment Inventory of Costs in Psychiatric Patients
PHQ-9: Patient Health Questionnaire
PTSD: Posttraumatic stress disorder
WAI-SR: Working Alliance Inventory–Short Form Revised
